### Procedures to prevent duplicate enrollments

To prevent participants from enrolling in the present study (RDS-ASTN), and also in RDS-CTTN, the present has its own name (“Brooklyn Community United,” or BCU) and recruitment coupons have a different color than those used in RDS-CTTN. The screening interview assesses whether participants are enrolled in the RDS-CTTN study, and the participant’s unique identifier is checked against a master database. Participants are informed during the consent process they may be withdrawn from the study if they have been previously enrolled in RDS-CTTN. Initial seeds to start peer recruitment will be recruited from the same HRA as the RDS-CTTN participants, but from the zip code with the fewest number of RDS-CTTN participants, as a means of tapping into network recruitment chains of individuals with no exposure to RDS-CTTN. Although we may not be able to eliminate duplicate enrollments, these procedures will greatly reduce their occurrence.

## Treat and Retain Phase (Confidential)

### Post-test counseling session for all participants

Participants return for their HIV test results approximately two weeks after the first session, and if found to be HIV infected, are presented with the opportunity to enroll in the Treat and Retain phase to receive support as they adapt to the new diagnosis, and link to HIV care in a timely fashion. They also receive compensation for peer recruitment at this time, which may encourage attendance at this appointment. (They can receive compensation for peer recruitment and decline to participate in the second session, however.) The session begins with elements either required or recommended by the CDC and local Department of Health for post-test HIV counseling. For participants whose test results are negative, the interventionist will address personal HIV risk/harm reduction; note CDC recommendations for annual testing; and will provide verbal instructions or a written referral directory for community-based HIV prevention services and other services (mental health care, substance use, housing). This session is brief (< 10 min) and will be the last study activity for HIV-negative study participants. Participants are compensated $15 for their time for this session.

For those who are found newly infected with HIV, the session is designed to provide post-test counseling. In addition, it will foster engagement into the Treat and Retain phase through demonstrated expertise of the interventionist with respect to HIV and HIV primary care, and continued use of the MI approach to build motivation to accept care navigation and support. This session will last approximately 60 min. Regarding post-test counseling, the interventionist will: provide the positive test result, and elicit and discuss reactions to the diagnosis, with a discussion of typical next steps for newly diagnosed individuals including adjustment, limited disclosure, HIV primary care, and reducing sexual and injection-related risk behavior. The interventionist will provide psychological support, ensure that the client has accurate information about steps necessary to prevent transmission; discuss with the participant whom to notify of his/her positive test result; offer assistance with short-term planning to cope with new diagnosis and emphasize the importance of HIV care. As a central aim of this study is to facilitate transition to the confidential Treat and Retain phase, which involves relinquishing anonymity, a portion of the session will be devoted to explaining this phase. To foster engagement, culturally targeted core messages will include: framing the problem of delayed linkage to care as a community issue (highlighting both racial/ethnic disparities in linkage to care and HIV outcomes, and progress made in linkage among populations of color); discussing multi-level barriers that individuals experience to HIV care, related to gender, substance use, low socio-economic status, and/or race/ethnicity; explaining what “confidential” means, including laws regarding reporting of names of newly diagnosed individuals to the local Department of Health (which is mandatory in our jurisdiction); providing handouts with activities and compensation; reviewing a menu of options and evoking benefits of each; and determining if the participant wishes to enroll in the Treat and Retain phase. All participants have the opportunity to engage in the lottery activity at this point.

Finally, we will make an HIV care appointment for the participant regardless of whether or not he/she enrolls in the Treat and Retain phase, consistent with local public health law. Participants who have not given their full name to the study can be put on the phone directly with the HIV care site and provide that information directly to the facility.

### Enrollment into the Treat & Retain Phase

Participants who are interested in enrolling in the Treat & Retain phase will next enter that phase of the study, beginning with signed informed consent and completing a locator form. Participants who are unsure whether they wish to enroll have a “grace period” of approximately three weeks to decide. They can contact the study to schedule an enrollment visit within that period. Compensation of $15 is provided for the second session.

### Care navigation

 Care navigation is a flexible and individualized intervention approach to reduce disparities in care for low income or marginalized populations [52, 53]. In practice, care navigation identifies and resolves the organizational, social, and individual barriers patients may experience to accessing services [54]. We will provide care navigation to newly diagnosed HIV-infected participants over a three- to six-month period, depending on the participant’s needs. During navigation, participants will be aided to identify and overcome barriers that they may encounter at various steps during the course of their linkage to HIV care. Navigation will consist of face-to-face meetings and phone contacts to provide participants with support, assistance making decisions about disclosing their HIV status, referrals, coordination of care, accompaniment to medical appointments, and assistance to get other necessary services or care. Only a limited number of face-to-face meetings will be compensated ($10, up to 5 compensated meetings in the first month) so as to not artificially increase navigation “dose.” Participants will be encouraged to contact the study outside of scheduled care navigation meetings/contacts for additional help or support, as needed. Duration and content of care navigation contacts are based on individual participant needs and will vary across participants, and will be logged to document their duration and content. We estimate that > 70 % of participants will be engaged in care by the end of three months. Those who are not engaged have the option of extending the care navigation period for an additional 3 months, for a total of 6 months of care navigation.

### Additional recruitment coupons

Individuals who test HIV-positive have the opportunity to recruit three additional peers during the care navigation phase, a type of network-based case finding [55, 56]. They will be encouraged to recruit their sexual and injection drug using partners, if they have not done so already.

### Medical Report Form and blood draw

At the end of the 6-month Treat and Retain phase, we will ask participants to have a Medical Report Form (MRF) completed by their HIV care provider. The Medical Report Form will contain health care appointment data abstracted from their medical chart, and will be signed by a health professional at the facility where the participant receives care. Participants can request that the form be filled out and return it to us, for which they will receive compensation ($25). Alternately, participants can request for us to contact the provider directly to obtain the data either over the phone, by secure fax or in person. Further, study staff will obtain a second set of blood specimens for CD4 and HIV viral load testing at the end of 6 months, and participants will be compensated $25 for this blood draw.

### Follow-up interview

At the end of the 6-month care navigation period, participants will be asked to participate in a brief follow-up interview assessing the health, relationship, and substance use indices assessed in the baseline interview, but focused on the past 6 months, as well as safety (social harms) and intervention acceptability. The follow-up interview will be conducted using the ACASI format ($30 compensation).

### Procedures for participants who are “known positives” (not shown on Fig. 2)

Individuals who report being HIV-infected during the screening interview and who meet the study’s eligibility criteria will provide verbal informed consent for and be enrolled in a track of the Seek and Test phase of the study. These participants will be asked to provide medical documentation of their HIV-positive status (which will be viewed but not retained); they will engage in a baseline interview that includes questions on their HIV history (e.g., date of first diagnosis with HIV), and receive a brief intervention session to orient them to the study and train them how to recruit peers. They will not be tested for HIV or receive other lab tests. Individuals who cannot provide medical documentation of their HIV-status will be enrolled in the main Seek and Test phase (described above), and offered participation in all of those activities. These HIV-infected participants who are not well engaged in care by DHHS definition [57] will be given the opportunity to enroll in the Treat and Retain phase of the study, for which they will provide signed informed consent. They will be asked to complete a Medical Report Form at the beginning and end of the Treat & Retain phase and will be provided with care navigation over three months. Compensation will be provided at the rates described above.

### Analysis plan

First, we will compare the yield of RDS-ASTN with the two other STTR strategies we described in a separate protocol, RDS-CTTN and VBS [27], with respect to newly diagnosed HIV infection. We will examine differences in demographic characteristics between VBS, RDS-CTTN and RDS-ASTN participants and adjust for these when comparing STTR approaches. Logistic regression will be used to compare the three STTR strategies on yield of newly diagnosed HIV infection. Covariates will include prior HIV testing.

Second, we will explore the feasibility of engaging RDS-ASTN participants who test HIV-positive into a confidential Treat and Retain study phase. Key indicators of feasibility will include the percentage of participants with HIV infection who accept the transition from the anonymous testing phase to the confidential Treat and Retain phase; and rates of engagement in Treat and Retain phase study activities. We also will explore the efficacy of the Treat and Retain components in terms of time to an HIV clinic appointment among newly identified HIV-infected HHR. We will describe the occurrence and timing of a first HIV clinic appointment and whether viral load and CD4 results were obtained. Cox proportional hazards regression will be used to compare STTR strategies (RDS-CTTN and RDS-ASTN) on the occurrence and timing of first HIV clinic appointment.

Third, we will project the clinical impact, costs, and cost-effectiveness of RDS-ASTN for identifying HHR, and linking them to and retaining them in HIV-related medical care. Incremental cost-effectiveness ratios (ICER) will be presented in terms of costs per HIV infection prevented and used to compare STTR strategies. We will estimate the costs and effectiveness outcomes for ICERs with projections from a mathematical model of HIV infections prevented, based on reductions in HIV risk behavior [58, 59] and viral load suppression associated with treatment [60, 61]. For outcomes not directly observed in participants recruited by RDS-ASTN, we will assume these are the same as for the RDS-CTTN intervention group; that is, an RDS-ASTN participant linked to care and retained for three months has the same probabilities of ART initiation and viral load suppression as an RDS-CTTN participant. The time horizon for our analysis is lifetime.

Finally, generalized linear models will be used to compare the socio-demographic, substance use, health, and HIV testing characteristics of those enrolled by RDS-ASTN with those in RDS-CTTN and VBS. This analysis will determine whether there are important differences in risk behavior and HIV testing history among these study groups, which may indicate differential effectiveness in reaching higher risk heterosexuals and those who have not tested or have tested infrequently.

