### Study population and sampling considerations

An estimated 750 participants will be recruited by peers and screened, and 500 of these will be enrolled. An estimated 45 % of the sample will be female. An estimated 60 % of the sample will be African American/Black, 35 % Latino/Hispanic, and 5 % White/non-Hispanic. We estimate that > 50 % of the sample will be substance users. Given estimates of HIV incidence and prevalence in the local National Behavioral Surveillance System studies [41], we expect to identify 65 participants with HIV infection, 40 (8 %) newly diagnosed and 25 previously diagnosed with HIV.

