### Hypotheses

The study will explore the following hypotheses: compared with VBS and RDS-CTTN, and controlling for potential differences on key socio-demographic characteristics across the samples, RDS-ASTN participants will have less HIV testing experience. Further, controlling for potential differences on key socio-demographic characteristics across the samples, RDS-ASTN will yield substantially higher rates of previously undiagnosed HIV compared with VBS and modestly higher rates compared to RDS-CTTN, although the RDS-ASTN intervention is less labor intensive than RDS-CTTN. This is because the brief and anonymous nature of the RDS-ASTN intervention may appeal to highly vulnerable individuals with multiple barriers to HIV testing. Further, we hypothesize that most participants (> 70 %) found to be HIV-infected in the RDS-ASTN intervention will engage in the Treat and Retain phase of the study, grounded in the efficacy of the MI approach combined with compensation based on behavioral economics principles to foster engagement. Last, we hypothesize that most participants in the Treat and Retain part (> 70 %), all of whom will be HIV infected, will be linked to care within 3 months, based on past studies of care navigation with similar populations [42, 43].

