### Individuals with previously diagnosed HIV infection

Participants who report they have previously been diagnosed as HIV infected during the screening interview, called “known positives,” may be enrolled in the study and may recruit peers. Indeed, HIV infected individuals may be an important link to those with undiagnosed HIV infection. HIV status will be confirmed with medical documentation by study staff by viewing one of the following: HIV diagnosis letter from a testing site; documentation of AIDS Drug Assistance Program coverage (a Federal program to provide HIV medications); a copy of the most recent HIV lab results or medical record including HIV diagnosis from a medical facility; current or recent antiretroviral therapy prescription or medication bottles; a signed and dated doctor’s note; or an M11Q, the New York State certification of an individual’s AIDS or HIV-symptomatic diagnosis. The type of documentation provided will be noted in a participant log. To preserve anonymity, the documentation will not be copied or retained by the study and no names or identifying information will be recorded. We have used these procedures to document HIV status in past studies [27, 46]. Study activities for those with known HIV infection are described below. In the next section we describe procedures for those who enter the study with an HIV-negative or unknown status.

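### The HIV-testing-history comparison includes people already diagnosed with HIV, who cannot show reach to the untested and can distort it if their share differs across the three samples

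*Protocol article*

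**What the plan says.** The last paragraph of the Analysis plan uses generalized linear models to compare several groups of characteristics, among them the "HIV testing characteristics of those enrolled by RDS-ASTN with those in RDS-CTTN and VBS". It names no exclusion. Differences are to be read as possible "differential effectiveness in reaching higher risk heterosexuals and those who have not tested or have tested infrequently". The Hypotheses section gives a direction: compared with VBS and RDS-CTTN, "RDS-ASTN participants will have less HIV testing experience", controlling for socio-demographic differences.

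People with a known HIV diagnosis belong to the enrolled group. The section on previously diagnosed infection says that they "may be enrolled in the study and may recruit peers" (only initial seeds must be HIV negative or of unknown status). The section on procedures for known positives says that they will "be enrolled in a track of the Seek and Test phase of the study", that "they will engage in a baseline interview that includes questions on their HIV history", and, for those with documentation, that "They will not be tested for HIV or receive other lab tests". The Baseline interview section lists testing history among the domains assessed. Of 500 enrolled, the sampling section expects "40 (8 %) newly diagnosed and 25 previously diagnosed with HIV".

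**The concern.** The comparison is meant to show whether anonymous single-session testing reaches people whom other testing misses. A person already diagnosed has been tested and found. On a measure of recent or current testing, such a person may look like someone who seldom tests, because there is little reason to test again after a diagnosis. On an ever-tested measure the same person counts as tested. Neither answer bears on reach to the untested.

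The planned adjustment does not deal with this, because it covers socio-demographic characteristics and a prior diagnosis is not one of them. Equal shares of known positives in the three samples cannot be taken for granted either. VBS recruits at public venues and the two RDS studies through peers. RDS-ASTN lets known positives recruit, and it gives those who test positive three further coupons. The share may thus depend on the recruitment method, which is part of what is being compared.

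**Working it through.** **Inputs from the article.** Enrolled in RDS-ASTN: 500. Expected known positives: 25, so 25/500 = 5 %. Power analysis section: about 80 % power for d = .19; α = .05 is stated for the odds-ratio comparisons.

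**Assumptions.** The α of .05 also applies here and is two-sided. The sizes of VBS and RDS-CTTN, their shares of known positives, and the testing measure with its look-back window are not given.

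**1. The plan's own figure.** With 500 in RDS-ASTN and a standard deviation of 1, the comparator size n that gives 80 % power at d = .19 solves

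1/n = (0.19 / (1.960 + 0.842))² − 1/500 = 0.00460 − 0.00200 = 0.00260, so n ≈ 385.

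The stated power is attainable, but the article does not allow it to be confirmed. The 385 is back-solved and is used below only as an assumption.

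**2. Upper bound on a recent-testing measure.** Suppose no known positive reports a recent test, the comparator holds none, and the true rate p among everyone else is the same in both samples. RDS-ASTN then shows 0.95p. The standardised shift is 0.05p / √(p(1−p)). The two-sided rejection rate with no true difference uses the standard error √(0.95p(1−0.95p)/500 + p(1−p)/385).

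| True p | RDS-ASTN shows | Standardised shift | Share of .19 | False-positive rate |
|---|---|---|---|---|
| 20 % | 19.0 % | 0.025 | 13 % | 7 % |
| 40 % | 38.0 % | 0.041 | 21 % | 9 % |
| 60 % | 57.0 % | 0.061 | 32 % | 15 % |
| 70 % | 66.5 % | 0.076 | 40 % | 20 % |
| 80 % | 76.0 % | 0.100 | 53 % | 30 % |

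On the arcsine scale the shifts at 40 % and 70 % are h = 0.041 and 0.075. For p = 40 %, the standard error is √(0.38·0.62/500 + 0.40·0.60/385) = 0.0331, the expected z is 0.020/0.0331 = 0.60, and the rejection rate is 9.3 %.

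**3. If the comparator also holds known positives.** With share g in the comparator, the spurious difference (RDS-ASTN minus comparator) is (g − 0.05)p.

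| g | p = 40 % | p = 60 % |
|---|---|---|
| 0 % | −2.0 points | −3.0 points |
| 2.5 % | −1.0 | −1.5 |
| 5 % | 0 | 0 |
| 8 % | +1.2 | +1.8 |

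**4. Ever tested.** Known positives all count as tested, so with none in the comparator RDS-ASTN shows 0.95p + 0.05. That is +1.5 points at p = 70 % and +0.5 at p = 90 %, against the hypothesis.

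**The case against.** A reader might infer that the analysis set pushes the result toward the hypothesis. The article does not support that. It would require fewer known positives in RDS-CTTN and VBS than in RDS-ASTN, and those shares are not reported. The section on previously diagnosed infection cites the VBS and RDS-CTTN protocol as one of the past studies that used the same procedures to document HIV status, so the comparators may include known positives too. Equal shares remove the artefact and a larger comparator share reverses it. No recency measure is named. For people who have never tested, the first of the two under-tested groups that the plan names, known positives work against the hypothesis; for lifetime test counts the direction is undetermined. That known positives stop testing is an inference: the article says only that this study will not test those with documentation, and a person diagnosed recently had a recent test. Zero recent testing is therefore an upper bound. All of this stands, and it limits the point to a conditional distortion.

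It can also be said that this is a secondary comparison in an exploratory, non-randomised study, and that a condensed article may leave exclusions for single variables to the full plan. The first lowers the weight of the point. The second carries less, because the article does state whom it compares (those enrolled), and where it wants a subset it names one: time to a clinic appointment is limited to newly identified infections.

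**Conclusion.** The point holds in a limited form and is minor. As written, the testing-history comparison includes about 5 % of RDS-ASTN participants whose history cannot bear on the conclusion to be drawn. It is distorted whenever the share of known positives differs across the samples.

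Neither the direction nor the size of any net bias is established. On recent or current testing it runs toward the hypothesis only if RDS-ASTN holds the larger share; on ever-tested it then runs against. The tabulated false-positive rates are upper bounds that rest on no recent testing among known positives, none of them in the comparator, no true difference, and an assumed comparator of 385. For true rates from 20 % to 80 % the artefact is at most about half of the detectable d = .19, so a reader should not infer that it could produce such a difference by itself.

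**What to change.** In the last paragraph of the Analysis plan, and for the testing-experience hypothesis, state that HIV testing history is compared, in all three samples, among participants who report no prior HIV diagnosis at screening. Describe known positives separately, with their number and share in each sample. Socio-demographic, substance use and health comparisons can stay on everyone enrolled.

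This is valid whatever the comparator shares prove to be. RDS-ASTN already asks about prior diagnosis at screening; whether RDS-CTTN and VBS recorded it in the same way should be confirmed.

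The cost is a line of wording and about 25 participants in this one comparison (475 instead of 500). Against a comparator of 385, the standard error becomes √(1/475 + 1/385) = 0.0686, so 0.19/0.0686 − 1.960 = 0.81. Power at d = .19 falls from 80.0 % to 79.1 %.
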